
**Fig. 1 Fig1:**
[figure not shown]
GAP Flow Diagram. Numbers and reasons of discontinuation of intervention and of lost to follow up will be given for each group

### Outcomes

*Primary outcomes,* which are assessed by questionnaires (survey data), are the quality of the patient-physician communication and patient informedness (Table 2). It is analysed whether values in the IG differ significantly from the CG.

**Table 2 Tab2:** Primary outcomes, instruments and measurement points

	t_0-physician_	t_0-patient_	t_1-patient_	t_2-patient_	t_1-physician_	t_2-physician_
Quality of the patient-physician communication (patient)						
Shared Decision-Making Questionnaire (SDM-Q-9) [38]			X			
Questionnaire on the communication behaviour of physicians (KOVA) [39]			X			
Scale “Satisfaction” of the P.A.INT-questionnaire [40–43]			X			
Quality of the patient-physician communication (physician)						
Scale “Effective and open communication” of the KOVA [39]^a,b^	X				X	X
Scales “Empathy”, “Openness and coherence”, “Positive regard and appreciation”, “Contact barriers” and “Satisfaction” of the P.A.INT-questionnaire [40–43]^a^	X				X	X
One Item of the Man-Son-Hing scale. [44]^a^	X				X	X
Shared Decision-Making Questionnaire (SDM-Q-Doc) [45, 46]^a^	X				X	X
Informedness (patient)						
Self-reported knowledge questionnaire^c^		X		X		
Self-reported knowledge global question^c^			X			
Perceived informedness questionnaire^c^				X		
Perceived informedness global question^c^			X			

^a^Instruments will be adapted so that physicians assess their communication behaviour across consultations

^b^Instrument will be adapted for assessing the communication from physician’s perspective

^c^These instruments will be developed for the project. The questionnaires will be checked for understandability and acceptance in a cognitive pretest using one-to-one interviews with eight patients having experienced back pain [47]

*Secondary outcomes* are assessed by questionnaires (survey data) and routine data from the insurance companies (Table 3). Secondary patient outcomes are self-reported self-efficacy regarding their own communication behaviour, health literacy, pain intensity, and days of sick leave and back pain related costs for the health care system. Since t0 and t1 of the patient survey are close together, outcomes of informedness, self-efficacy, and health literacy at t1 are only assessed via global questions. Secondary outcomes for physicians in the IG are the concordance of provided and needed information, the usability of the platform and their actual use of it. Correlation of physician and patient data is possible, as the used items and questionnaires are similar. Differences between CG and IG are additionally analysed regarding the secondary outcomes. Table 3 also contains additionally assessed variables.

**Table 3 Tab3:** Secondary outcomes and control variables

	t_0-physician_	t_0-patient_	t_1-patient_	t_2-patient_	t_3-patient_	t_1-physician_	t_2-physician_
Secondary outcomes (survey data)							
Self-reported self-efficacy (patient)							
Perceived Efficacy in Patient-Physician Interactions (PEPPI)-Questionnaire [48]		X		X			
One Item of Perceived Efficacy in Patient-Physician Interactions (PEPPI)-Questionnaire [48]			X				
Health Literacy (patient)							
Health Literacy Questionnaire (HLQ) [31, 49]		X		X			
Health literacy global questions			X				
Pain intensity (patient)							
Visual analog scale (VAS) [50]		X		X			
Accordance of provided and needed information (physician)							
Domains “Adequacy of information” and “Usability of information” of the Decision Attitude Scale^a,b^ [51]						X	
Self-developed item whether content fits expectations						X	
Usability (physician)							
System Usability Scale (SUS)^a,b^ [52]						X	
Self-developed items on usability						X	
Use of portal (physician)							
Self-developed items on actual use of portal^b^						X	X
Secondary outcomes (routine data)							
Patient’s days of sick leave					X		
Patient’s back pain related costs for the health care system					X		
Control variables (survey data)							
Patient							
Back Belief Questionnaire [53]		X					
Sociodemographic data		X	X	X			
Internet Use		X					
Medical data		X		X			
Physician							
Sociodemographic data	X						
Structural features of the practice (kind of practice, patients per quarter, number of employees, location and region)	X						
Control variable (web analytics)							
Portal use by patients		Throughout the intervention phase (after consultation)					
Portal use by physicians	Throughout the intervention phase						

^a^Instrument will be adapted so that the physicians assess the portal

^b^only intervention group

#### Sample size calculation

A priori calculation of the sample size to test the IG’s superiority to the CG in primary outcomes (comparison of adjusted mean values in two groups) was performed with the software *“Power and Precision*”. We used an effect size of 0.30, power of 0.80 and a Bonferroni adjustment (5% / 2 = 2.5%) due to the multiple testing of two primary outcomes. The design effect due to clustering of the practices [30] is DE = 1 + 0.01 × (10–1) = 1.09 with an assumed intra-cluster correlation of 0.01 [31] and a number of cases per cluster of *N* = 10. With a 2:1 distribution in the IG and CG, a sample size of *N* = 320 (IG) and *N* = 160 (CG) without design effect and *N* = 349 (IG) and *N* = 175 (CG) with design effect was calculated. Due to an expected dropout of approximately 35% a sample size of *N* = 537 (IG) and *N* = 270 (CG) is necessary. However, health economics evaluation including a budget impact analysis requires a relatively large variance of cost values (150% standard deviation). Based on a power of 0.80, an alpha level of 5% and an effect size of 30%, the number of cases is *N* = 590 (IG) and *N* = 295 (CG) without design effect and *N* = 643 (IG) and *N* = 322 (CG) with design effect. Given the assumed dropout of approximately 35%, this results in the desired recruitment target of *N* = 1.000 (IG) and *N* = 500 (CG).

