## Methods

The GAP trial uses a prospective multi-centre, cluster-randomized parallel group design in order to evaluate whether the use of the GAP portal on back pain is superior to routine care. The GAP project consists of three phases. (1) Within the pilot phase, the portal will be tested for usability by physicians and patients and adapted according to the pilot findings (Additional file 1: Development and piloting of the GAP portal). (2) The main trial (second phase) evaluates the effects on pre-defined outcomes in general practitioners and patients with back pain (Table 1). (3) Within the third phase, the potential benefit of web-based information for health problems other than back pain will be analysed (Additional file 2: Expanding of the GAP portal).

**Table 1 Tab1:** PICO question of the GAP trial

Research Question	What are the effects of using the back pain internet portal compared to standard care in patients with back pain?
Population	150 general practitioners and 1500 back pain patients in Northern Bavaria
Intervention	Using the portal during (physician) and after (patient) the consultation.
Comparison	Routine consultation (no use of the portal)
Outcomes	1. Physicians‘and patients’ informedness 2. Physician-patient-communication 3. Patients‘health literacy and self-efficacy expectation 4. Days of sick leave 5. Back pain related health costs

*Hypothesis on primary outcomes:* (1) After the consultation, the informedness and the quality of the physician-patient communication are rated significantly higher by general practitioners and patients who use the portal (intervention group, IG) than by those who do not (control group, CG, consultation as usual).

*Hypotheses on secondary outcomes:* (2) 3 weeks after the consultation, the patients’ informedness, health literacy and self-efficacy are significantly higher among those who use the portal than among those who do not. (3) 3 months after consultation, the number of days of sick leave as well as the utilization of health system resources is significantly lower among patients who use the portal than among those who do not.

*Design:* Prospective cluster RCT with pre-, post- and one follow-up-measurement and process evaluation.

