### Participants and recruitment

Together with the *Bavarian Association of Family Physicians and General Practitioners,* the *Institute of General Practice at the University Medical Center Erlangen* (UHE) will recruit a total of 150 general practitioners (GP) from practices in Northern Bavaria. Two-thirds of the practices are randomized to the IG and one third to the CG. If a GP practice expresses interest after being invited to participate in the study, it receives information concerning the study, regulations for enrolling in the intervention program, and participation documents for the GP practice and the patients. After written consent to study participation and enrolment in the intervention program, the practice is formally included in the GAP trial. The UHE passes on registration data to the *Bavarian State Association of company health insurance fund*, which is responsible for the cooperation with the participating company health insurance funds. Over five quarters (July 2018 to September 2019), the GP practices are to recruit a total of 1000 patients for the IG and 500 for the CG. With an average share of at least 20% BKK insured persons, 900 patients per practice license in Bavaria and a back pain prevalence of almost 30%, the resulting recruitment potential is 50 to 60 patients per physician. The fact that physicians receive reimbursement for recruitment and patients receive a book voucher will facilitate sufficient recruitment.

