#### Analysis of physicians‘questionnaire data

The data analysis is primarily exploratory. The primary outcomes will be analysed using inferential statistics methods. IG and CG will be compared across the three measurement points. Statistically adjusted comparisons of means between IG and CG as well as across the three measurement points (using propensity scores) will be conducted. The characteristics of the practices and the user data of the online platform will be used as control variables. Before the calculations, the missing data processes, singular missing data and the drop-out of patients will be analysed. Recommendations regarding the handling of missing data in order to correct information biases will be considered [33]. If data is missing completely at random or missing at random, missing data will be imputed using the expectations-maximation algorithm. Moreover, there will be sensitivity analyses to assess the influence of missing data processes.

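### The 80% power stated for the primary outcomes holds for patient ratings only; physician-rated communication, also primary, has at most 150 raters and about 31% unadjusted power on the same inputs

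*Protocol article*

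**What the plan says.** The section Sample size calculation presents its computation as "A priori calculation of the sample size to test the IG’s superiority to the CG in primary outcomes", without saying whose ratings are meant. It takes an effect size of 0.30, "power of 0.80 and a Bonferroni adjustment" to 2.5% for two primary outcomes, a 2:1 allocation, 10 cases per cluster and an intra-cluster correlation of 0.01. It arrives at 320/160, then 349/175 with the design effect, and 537/270 after 35% dropout. The final target of 1000/500 patients comes from the health economic calculation.

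Physician ratings are treated as primary in four places:

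- The hypothesis on primary outcomes (Methods) states that "the informedness and the quality of the physician-patient communication are rated significantly higher by general practitioners and patients who use the portal".
- Table 2 (Outcomes), which lists the primary outcomes, has a block whose heading begins "Quality of the patient-physician communication (physician". It holds four instrument rows, each measured at physician t0, t1 and t2.
- Procedures for physicians describes the forms that physicians complete at those three time points as the primary outcome questionnaires.
- Analysis of physicians' questionnaire data says: "The primary outcomes will be analysed using inferential statistics methods". The sentence before it calls the physician analysis mainly exploratory.

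On the number of physicians, Participants and recruitment says that the general practice institute "will recruit a total of 150 general practitioners (GP) from practices in Northern Bavaria". A footnote to Table 2 fixes the unit of rating: "Instruments will be adapted so that physicians assess their communication behaviour across consultations".

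**The concern.** A physician scores his or her own communication once per time point, across consultations. Enrolling 1500 patients therefore adds nothing to the number of physician ratings, which is at most 150. A power statement made for the primary outcomes as a whole is then read as covering an outcome for which the design does not deliver that power. If an effect of the planned size exists among physicians, the most likely result is still non-significant. A reader who trusts the published 80% could take that result as evidence against an effect. The text also leaves open whether this outcome is confirmatory, because it is primary in Table 2 and in the hypothesis but described as mainly exploratory in the analysis section.

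**Working it through.** **Inputs from the protocol article.** Effect size d = 0.30 (SD = 1), power 0.80, alpha 2.5% per primary outcome, allocation 2:1, design effect 1.09, dropout 35% (Sample size calculation); 150 physicians (Participants and recruitment); 10 questionnaire packages per physician (Procedures for patients). Sidedness is not stated. Two-sided is inferred because only that choice reproduces the printed numbers.

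**Step 1: reproduce the plan's figure.** For 2:1 allocation the control-group size is

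n(CG) = 1.5 × (2.2414 + 0.8416)² / 0.30² = 1.5 × 9.505 / 0.09 = 158.4, so 159, with 318 in the IG.

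The plan prints 160/320, which agrees within rounding. Power at 320/160 is 80.4%. Two-sided 5% or one-sided 2.5% would give 131/262, and one-sided 5% would give 104/208; neither matches. Then 320 × 1.09 = 348.8 and 160 × 1.09 = 174.4 (printed 349/175), and 349/0.65 = 536.9 and 175/0.65 = 269.2 (printed 537/270). The arithmetic is sound.

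**Step 2: identify the unit.** Ten cases per cluster matches the 10 patient packages per physician, and 480 subjects before inflation exceeds the 150 physicians planned. The counted unit is the patient.

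**Step 3: apply the same inputs to physicians.** Two thirds of the practices go to the IG, so about 100 versus 50 physicians are expected.

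- All 150 physicians: SE = √(1/100 + 1/50) = 0.1732. Power = Φ(0.30/0.1732 − 2.2414) = Φ(−0.51) = 30.5% (noncentral t: 30.0%).
- With 35% dropout, which the article gives for patients and is assumed here for physicians, 65 versus 32.5: SE = 0.2148. Power = Φ(1.396 − 2.2414) = Φ(−0.845) = 19.9% (noncentral t: 19.4%).

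**Step 4: detectable effect at 80% power.** (2.2414 + 0.8416) × SE = 0.53 SD with all 150 physicians and 0.66 SD with 35% dropout, unadjusted.

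**Step 5: sensitivity to adjustment for the t0 score.** With an assumed correlation r between baseline and outcome, the SD becomes √(1 − r²). The correlations are assumptions; the article gives none.

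| Assumed r | alpha 2.5%, no dropout | alpha 2.5%, 35% dropout | alpha 5%, no dropout | alpha 5%, 35% dropout |
|---|---|---|---|---|
| 0 | 31% | 20% | 41% | 29% |
| 0.5 | 40% | 26% | 52% | 36% |
| 0.7 | 57% | 39% | 68% | 50% |
| 0.8 | 74% | 53% | 82% | 64% |

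The detectable effect shrinks by the same factor. With all 150 physicians it is 0.53 × 0.866 = 0.46 SD at r = 0.5 and 0.53 × 0.714 = 0.38 SD at r = 0.7.

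**Step 6: patient ratings, for contrast.** With 1000/500 recruited and 35% lost, 650/325 remain. After the 1.09 design effect, power at d = 0.30 and 2.5% is about 98%. The patient-rated outcomes are not affected.

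**The case against.** **The calculation is visibly about patients.** The cluster size and the recruitment targets show this to a careful reader, and the article nowhere says that 80% applies to 150 physicians. That is fair. The defect is an unqualified phrase, and no number is miscalculated. But the phrase covers all primary outcomes, and one of them is rated by physicians.

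**The physician analysis is called mainly exploratory.** This softens the point, and using inferential methods does not by itself make an analysis confirmatory. It does not resolve the conflict, because the next sentence singles out the primary outcomes for inferential analysis, and neither Table 2 nor the primary hypothesis carries a qualification.

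**Adjustment raises power.** Physicians are measured at t0 and adjusted comparisons are planned, so the unadjusted 31% need not be the final figure. This stands, and it is why a range is shown. The gain depends on correlations that the article does not give. The sample size section already speaks of adjusted means, so its 0.30 may already refer to the adjusted scale, in which case there is no further gain. Of the cases computed, none reaches 80% at 2.5%. Only r = 0.8 with no dropout and a 5% alpha does.

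**Stronger readings that the article does not support.** A reader might infer that half of the primary hypothesis is underpowered. Table 2 has three blocks (communication by patients, communication by physicians, informedness of patients), and one of them is affected. A reader might also infer that physicians' clustering within practices will be ignored, since the physician section names no practice effect. A condensed article's silence on a model term is not a decision, and the term may be specified elsewhere. Clustering is supporting only: with an assumed 2–3 physicians per practice and an assumed intra-cluster correlation of 0.01–0.10, unadjusted power at 2.5% with no dropout would be 25–30% instead of 31%.

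**Conclusion.** The point holds as one of scope and consistency. The stated 80% power is a property of the patient-rated outcomes. For physician-rated communication the design gives about 31% with the plan's effect size and alpha, all 150 physicians and no baseline adjustment. This rests on three assumptions: d = 0.30 applies to physicians too, the test is two-sided at 2.5%, and the split is close to 100:50.

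A reader might take 20–31% as the physician power outright. The article does not support that. The 20% end borrows the patient dropout figure, and both ends leave out the t0 score. Assumed correlations of 0.5–0.7 give about 26–57%, depending on dropout, and 0.8 without dropout gives about 74%. What can be said firmly is that power falls short of 80% at the plan's alpha in every case examined. It should be corrected before results are known, because the statement credits a primary outcome with power that the design lacks, and restating its scope is cheap.

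**What to change.** 1. In Sample size calculation, say that the 80% power and the numbers 320/160, 349/175 and 537/270 refer to patient-rated primary outcomes.
2. Settle the status of physician-rated communication in one of two ways. Either declare it exploratory or secondary, in line with the analysis section, and adjust Table 2 and the primary hypothesis to match. Or keep it primary and state its own power or detectable effect: about 0.53 SD unadjusted with all 150 physicians, 0.66 SD with an assumed 35% dropout, smaller with t0 adjustment at a stated correlation.
3. Use the t0 physician score, which is already collected, as a covariate in the physician comparison.

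No additional physicians or data are needed. The cost is a less favourable power statement for one primary outcome. If that outcome is relabelled, the trial is registered and the section Protocol amendments requires substantial changes to the evaluation to be documented and reported to the ethics committee and in the main publication, so this is a formal amendment. Keeping the label and stating the physician power is the less intrusive route.

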### Statistical methods

#### Analysis of patients‘questionnaire data

Based on the analysis of the missing outcome data, simple or multiple imputation may be considered. Dropout analysis will be performed using Chi-Squared tests for nominal variables, Mann–Whitney U tests for ordinal variables and t-tests for interval variables. The significance level is set at *p* = 0.05. Special attention is paid to the hierarchical data structure of the questionnaire data. Due to the cluster randomisation, patients’ responses cannot be presumed as independent, as the patients are nested within practices. Because of this, separate two-level (patient – practice) multilevel linear models for both measurement points (t1 and t2) will be calculated. Treatment allocation (IG vs. CG) will be used as predictor variable in the multilevel linear models. The fit of the multilevel linear models are tested using amongst others the Akaike’s information criterion and Schwarz’s Bayesian criterion. Despite the randomisation a propensity score adjustment is considered in case of a potential imbalanced allocation [32]. Intraclass correlations are calculated to assess the cluster (practice) dependency of the responses.

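### Alpha is split for two primary tests, but Table 2 labels seven post-baseline patient measures as primary and nothing reduces them to two

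*Protocol article*

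**What the plan says.** The section on sample size plans "to test the IG’s superiority to the CG in primary outcomes (comparison of adjusted mean values in two groups"), and the level comes from "a Bonferroni adjustment (5% / 2 = 2.5%) due to the multiple testing of two primary outcomes". The other inputs are "We used an effect size of 0.30, power of 0.80" and 2:1 allocation.

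The Outcomes section names two primary outcomes, communication quality and patient informedness, refers to Table 2, and adds: "It is analysed whether values in the IG differ significantly from the CG". Table 2 lists the following after baseline.

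- **Patients, communication, t1:** SDM-Q-9, KOVA, and the P.A.INT Satisfaction scale.
- **Patients, informedness, t1:** one global question on knowledge and one on perceived informedness.
- **Patients, informedness, t2:** the knowledge questionnaire and the perceived informedness questionnaire.
- **Physicians, communication, t1 and t2:** one KOVA scale, five P.A.INT scales, one Man-Son-Hing item, and SDM-Q-Doc.

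For the patient data, separate "multilevel linear models for both measurement points (t1 and t2) will be calculated". In the same section, directly after the dropout tests, comes "The significance level is set at" p = 0.05. No other level appears there.

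The hypotheses at the start of Methods place the primary effect after the consultation, for general practitioners as well as patients. They list patient informedness at three weeks under the secondary outcomes. The section on physician data calls that analysis mainly exploratory, but has its primary outcomes tested inferentially.

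**The concern.** A Bonferroni split by two protects two tests. It gives 5% overall only if one test is made per domain. The article does not say which instrument, or which combination of instruments, stands for each domain. The analysis text points to several tests, because it models t1 and t2 separately. The health economic section also treats self-reported knowledge and perceived informedness as two quantities, each with its own cost-effectiveness ratio, so informedness is not handled as one variable.

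The stake is the confirmatory claim. If a significant result on any listed patient measure may be reported as success on a primary outcome, the chance of a false claim exceeds 5%. The outcomes are self-reported, and participants and evaluators are not blinded. A lead measure left open could therefore be chosen with the results in view. The article makes wider release of the portal depend on proven benefit.

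**Working it through.** **1. The plan's own figure.** Inputs from the sample size section: standardised difference d = 0.30, power 0.80, level 0.025, 2:1 allocation. With the normal approximation, n(CG) = (z[1−α/2] + z[0.80])² × 1.5 / d².

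- Two-sided 0.025: (2.241 + 0.842)² × 1.5 / 0.09 = 158.4, so 159 and 318. The noncentral t version gives 160 and 320, exactly as stated.
- Two-sided 0.05 or one-sided 0.025: 131 and 262. One-sided 0.05: 104 and 208. Neither matches.
- Design effect: 320 × 1.09 = 348.8 and 160 × 1.09 = 174.4, stated as 349 and 175. Dropout: 349 / 0.65 = 537 and 175 / 0.65 = 270, as stated.

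The arithmetic is sound. It fixes the level at two-sided 2.5%, that is, at exactly two tests.

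**2. Count of patient measures in Table 2.** Communication at t1: 3. Informedness at t1: 2. Informedness at t2: 2. This makes 5 at t1 and 7 in all. If three-week informedness is secondary, as the hypotheses say, the count is 5.

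**3. Family-wise error with each measure at 2.5% and any one success counting.** For m independent tests it is 1 − 0.975^m. For equally correlated normal test statistics with correlation ρ, it is the probability that the largest of m absolute values exceeds 2.241, found by numerical integration. The documents give no correlations, so the values of ρ are assumptions.

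| Measures | Independent | ρ = 0.5 | ρ = 0.7 | ρ = 0.9 |
|---|---|---|---|---|
| 2 (as split) | 4.9% | 4.7% | 4.3% | 3.6% |
| 5 (patient, t1) | 11.9% | 9.8% | 8.0% | 5.4% |
| 7 (patient, t1 and t2) | 16.2% | 12.6% | 9.8% | 6.1% |

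Only the two-test row stays within 5%.

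**4. Adjusting over all seven instead.** The level is 0.05 / 7 = 0.00714, with z = 2.690.

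- Required size: (2.690 + 0.842)² × 1.5 / 0.09 = 208 CG and 416 IG. With the design effect this is 227 and 454, and with 35% dropout 349 and 698. Both are below the recruitment target of 500 and 1000, which the cost outcome sets.
- Power per measure at that target: the effective CG size is 500 × 0.65 / 1.09 = 298.2, and Φ(0.30 × √(298.2 × 2/3) − 2.690) = Φ(1.54) = 94%.
- Power per measure at the plan's 160 and 320, before the design effect: 66%. The room comes from the cost-driven target, not from the primary-outcome calculation.

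**The case against.** The strongest reply is that Table 2 separates outcomes from instruments. Two constructs with several instruments each is consistent with two primary outcomes, and the lead instrument or composite may be set in an analysis plan that is not shown. No text says that any single instrument suffices, and hypothesis (1) is worded jointly. If every measure had to succeed, the error would not be inflated.

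Part of this stands. The error rates above are conditional on an any-one-success rule within a domain, which the article does not state. But a rule that all must succeed would need no Bonferroni split, so the split itself points to success on either outcome. The point also does not rest on missing detail: the article states a two-test correction and, beside it, a primary list that is longer than two and partly contradicted by its own hypotheses.

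Two stronger readings are tempting, and the article does not support either as fact.

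- **Primary tests run at 5%.** A reader might infer this from the p = 0.05 sentence. It directly follows the dropout tests and probably refers to them. Still, it is the only level in that section, so it needs clarifying.
- **Twenty-three confirmatory tests.** Adding 8 physician scales or items at two time points gives 7 + 16 = 23, and 1 − 0.975^23 = 44%. This figure assumes independence and full confirmatory status for the physician measures, yet their analysis is called mainly exploratory. It also assumes one test per time point, although that section compares the groups across all three measurement points. Their status is ambiguous, because hypothesis (1) includes practitioners and the section tests primary outcomes inferentially. They would raise the error further if confirmatory, but the patient measures alone carry the point.

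Independence is also unrealistic for questionnaires that one patient completes about one consultation. The correlated columns are the more plausible ones.

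**Conclusion.** The stated error control does not match the plan's own list of primary measures. At 2.5% per measure, with any one success counting, the family-wise error on the patient side runs from about 5.4% (five measures, assumed correlation 0.9) to 16.2% (seven measures, independent), against an intended 5%. At an assumed correlation of 0.5 it is about 10% for five measures and 13% for seven. The direction is the same throughout this range; the size depends on the assumed correlation and on the unstated success rule.

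Two inconsistencies add to this: three-week patient informedness is secondary in the hypotheses and primary in Table 2, and the physician measures are both primary and mainly exploratory. The sample size is not at fault. It is correct for two tests, and the recruitment target leaves room for more. The matter should be settled before the data are analysed.

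**What to change.** 1. Reconcile the hypotheses with Table 2 on whether patient informedness at three weeks is primary or secondary.
2. Before analysis, name for each of the two domains one patient-rated measure, or a pre-specified composite, and one time point consistent with hypothesis (1). An example is one communication measure and one informedness measure, both at t1.
3. Test each at two-sided 2.5%, or use Holm over the two.
4. Label all other Table 2 measures, including the physician ones, secondary or exploratory.
5. In the section on patient data, state that the primary tests use 2.5% and that 0.05 applies to the dropout and secondary analyses.

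The alternative is to keep all seven patient measures primary and apply Holm or Bonferroni over seven. Under the plan's effect size, ICC, cluster size and dropout, the 1000 and 500 target gives about 94% power per measure.

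Both routes change wording only and need no further data. The price is that fewer measures carry the primary label, or that each faces a stricter threshold.
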